Persons who fall into any of the following categories shall not be used as research subjects.

1. Complications of cardiac disease.
2. Cardiac pacemaker users
3. History of epilepsy
4. Visual acuity (correctable) less than 0.7 in both eyes
5. Air conduction hearing greater than 30㏈.
6. There is tactile hypoesthesia (unable to perceive Semmes-Weinstein monofilament no. 2.83)
7. Perceived significant taste and olfactory abnormalities
8. History of any other visual or hearing impairment, language comprehension disorder, mental disorder, or motor dysfunction that would interfere with the performance of the research task.

The reasons for setting (a) and (b) are because they may affect autonomic measurements and (c) because they may affect electroencephalography measurements. The reason for (d) through (g) is to exclude people with functional abnormalities in the sensory organs to be evaluated and intervened in this study.

Suspension Criteria

1. When the research subject wishes to discontinue
2. When it is deemed appropriate to discontinue other activities.

3) Number of research subjects and rationale for setting the number of research subjects

The target number of patients for this study is 58, consisting of 29 in the intervention group and 29 in the control group.

Regarding the rationale for the setting, this study will conduct a two-group comparison (unpaired t-test, one-tailed) of the intervention and control groups for changes in the parasympathetic index (RSA: respiratory sinus arrhythmia) before and after the intervention as the main outcome. Using G*Power 3.1.9.2 and referring to previous studies^11)12)^ that utilized RSA, the effect size was set to 0.7, with an alpha error of 0.05 and a beta error of 0.20, resulting in a total sample size of 52 participants. In addition, considering the possibility of approximately 10% dropout, approximately 58 subjects will be needed for the study. 58 subjects will be randomly divided into 29 in the SRI group and 29 in the control group.

The number of subjects in the previous study^6)13)^, which investigated parasympathetic indices and sensory processing characteristics in children with ASD and normal children, was 50 and 83, respectively, and we believe that the above number of subjects is generally appropriate.

5. Method of the study and the scientific rationale for the study

1) Design

□ Intervention study

Phase of study: Exploratory study

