The experimental flow is shown in Figure 2. The evaluation and intervention will be conducted over three days: on the first day, after explanation and consent, a preliminary survey and initial evaluation will be conducted; on the second day, the evaluation immediately before the intervention, the intervention, and the evaluation immediately after the intervention will be conducted; and on the third day, the final evaluation will be conducted. Each evaluation item will be conducted with appropriate breaks in between.

[figure not shown]

Figure 2: Measurement schedule

4) Summary of analysis

- - Primary Endpoint

(a) Differences in the variability of RSA values due to sensory stimulation of SCP before and after the intervention.

- - Secondary endpoint

(a) EEG amplitude differences before and after intervention, (b) POMS2 score differences before and after intervention, (c) CAB score differences at initial and final assessment, (d) correlation between AQ scores and RSA values, (e) correlation between SPQ scores and RSA values, (f) correlation between A/ASP scores and RSA values, (g) power spectrum by EEG band during intervention, (h) RSA power spectrum of each EEG band, (h) RSA during intervention

- - Main Analysis Methods

The statistical significance level is set at p < 0.05. A one-tailed test is used.

Basic information, medical information, and observation records during the use of the sensory room were compiled as descriptive statistics: RSA values were calculated as the difference between the SCP resting period and the mean value during each sensory stimulus; EEG amplitudes were obtained by subtracting the standard stimulus waveform from the deviant stimulus waveform of the presented task to obtain the amplitude of the positive or negative component during latencies of approximately 200 to 400 ms. The EEG amplitude is obtained by subtracting the standard stimulus waveform from the deviant stimulus waveform of the presented task.

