Unpaired t-tests will be conducted between the two groups to confirm the absence of any differences between the SRI and control groups in the baseline pretest, initial assessment, and the assessment immediately before the intervention. Next, we will compare the differences in RSA values, EEG amplitude, and POMS2 scores between the two groups at the immediately pre-intervention and immediately post-intervention assessments using an unpaired t-test. The differences in CAB scores between the initial and final assessments will be compared between groups using an unpaired t-test. If there is a significant difference between the two groups in the items measured at baseline, stratified or subgroup analyses will be conducted.

Additionally, correlation coefficients will be determined for the association between the AQ, SPQ, and A/ASP scores from the preliminary study and the differences in RSA values, EEG amplitude, and POMS2 scores at the time of the evaluation immediately before and immediately after the intervention. For cerebral blood flow, the difference between the mean values at the beginning and end of each 5-minute period in the two groups at the beginning and end of the intervention will be calculated and compared between the groups using an uncorrelated t-test.

For the measures during the intervention, t-tests with no correspondence between groups will be performed for the power spectrum per band of the EEG and the RSA.

6. Research period

1) Research subject enrollment period

　Four years from the date of approval by the head of the research institution.

2) Study subjects observation period

　　　The observation period for research subjects will be 3 days from the time of the preliminary survey.

3) Research implementation period

The research period is five years from the date of approval by the head of the research institution.

7. Procedure for obtaining informed consent ("IC")

Before the preliminary study, the subject will be fully informed about the study using a written explanation of the study. The measurement items, measurement time, intervention details, and non-invasive nature of the study will be explained, and the subject will then decide to participate of his/her own free will. The subject's consent to participate in the study and his/her signature constitute the informed consent procedure.

8. Handling of personal information, etc.

1) Types of personal information, such as materials and information handled in the research

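### Outcomes are compared by t-tests on raw before-after differences; adjusting for the pre-value already collected would give more power at the same sample size and remove the effect of chance imbalance in that pre-value

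*Protocol*

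**What the plan says.** Protocol section 5, item 4) (Main Analysis Methods) fixes the comparison for three outcomes: "we will compare the differences in RSA values, EEG amplitude, and POMS2 scores between the two groups", from the assessment immediately before the intervention to the one immediately after, by unpaired t-test. CAB follows the same pattern: "The differences in CAB scores between the initial and final assessments will be compared between groups using an unpaired t-test". The level and direction are also set there: "The statistical significance level is set at p < 0.05. A one-tailed test is used".

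Section 4, item 3) sizes the trial on the same test, a "two-group comparison (unpaired t-test, one-tailed) of the intervention and control groups for changes in the parasympathetic index". The standardised difference is given first: "the effect size was set to 0.7". The error rates and the total they lead to come next: "with an alpha error of 0.05 and a beta error of 0.20, resulting in a total sample size of 52 participants". Dropout of about 10% brings the total to 58, or 29 per arm.

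Section 5, item 2) shows that RSA, EEG and POMS2 are measured on the intervention day before and after the session, and CAB on the day before and the day after. Every outcome in these comparisons therefore has a pre-value.

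No baseline covariate is mentioned. The only provision for imbalance is a set of t-tests on baseline items, followed by stratified or subgroup analyses if one is significant.

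**The concern.** A t-test on change is a regression of the post-value on arm with the slope on the pre-value forced to be 1. With similar pre and post variances the true slope is ρ, which is below 1. Forcing it to 1 has two effects.

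- **Lost precision.** The change score carries the noise of both measurements. ANCOVA estimates the slope and removes only what the pre-value predicts.
- **Sensitivity to chance imbalance.** If one arm starts higher by chance, regression to the mean moves its change score for reasons unrelated to treatment.

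Both are larger when ρ is low. Under Main Analysis Methods, the RSA value is itself a difference between rest and stimulus, and EEG amplitude is a deviant-minus-standard difference. Such scores often repeat less well than raw levels, so a high ρ should not be presumed. At stake is precision the trial has already paid for, and a pre-specified answer to baseline imbalance in place of one triggered by the data.

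**Working it through.** **Inputs.** From the protocol: d = 0.7 on the RSA change, one-tailed α = 0.05, power 80%, 1:1 allocation, 52 analysed, 10% dropout. Assumed, because the protocol does not give it: the pre-post correlation ρ, shown from 0.3 to 0.95. Equal pre and post SDs (s) are also assumed.

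**1. The protocol's own figure.** Noncentral t with 26 per arm: noncentrality 0.7 × √(26/2) = 2.52, df = 50, one-tailed power 80.1%. So 26 per arm, 52 in total; 52/0.9 = 57.8, rounded up to 58. Both figures reproduce.

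**2. Variance of the two analyses** (per participant):

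- change score: 2s²(1 − ρ)
- ANCOVA: s²(1 − ρ²)
- ratio, ANCOVA to change: (1 − ρ²)/[2(1 − ρ)] = (1 + ρ)/2

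Without equal SDs, the change-score variance exceeds the ANCOVA variance by (s_pre − ρ·s_post)², which is never negative. Apart from the cost of estimating one slope, ANCOVA cannot be the less precise of the two.

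**3. Power at 26 per arm.** Effective d = 0.7/√[((1 + ρ)/2) × (1 + 1/48)]. The factor 1 + 1/(N − 4) allows for a random covariate, and df = 49. The last column is the total N needed for 80% power before dropout.

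| ρ | Variance ratio | Effective d | One-tailed power | N for 80% |
|---|---|---|---|---|
| planned t-test | 1 | 0.700 | 80.1% | 52 |
| 0.3 | 0.65 | 0.859 | 92.1% | 36 |
| 0.5 | 0.75 | 0.800 | 88.5% | 42 |
| 0.7 | 0.85 | 0.751 | 84.8% | 46 |
| 0.8 | 0.90 | 0.730 | 82.9% | 48 |
| 0.9 | 0.95 | 0.711 | 81.1% | 52 |
| 0.95 | 0.975 | 0.702 | 80.2% | 52 |

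Without the random-covariate factor, the figures at ρ = 0.3, 0.5 and 0.7 are 92.5%, 89.0% and 85.4%.

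A simulation with 10,000 runs per ρ agrees (change-score t-test against ANCOVA): 79.5% v 91.4% at 0.3, 80.4% v 88.8% at 0.5, 80.2% v 84.7% at 0.7, 80.0% v 81.0% at 0.9, and 80.8% v 80.1% at 0.98.

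Holding d = 0.7 on the change scale means that the raw effect, 0.7 × √[2(1 − ρ)] × s, differs by row: 0.83 SD at ρ = 0.3, 0.70 at 0.5 and 0.54 at 0.7. Each row compares the two analyses at that ρ; the rows are not one fixed raw effect seen at different correlations.

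**4. Chance imbalance.** The standard error of the baseline difference is √(2/26) = 0.28 SD. Given an imbalance b, the change-score contrast is displaced by (1 − ρ)b in size. For b = 0.3 SD:

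- ρ = 0.3: 0.21 SD, and 0.21/0.83 = 25% of the assumed effect
- ρ = 0.5: 0.15 SD, and 0.15/0.70 = 21%
- ρ = 0.7: 0.09 SD, and 0.09/0.54 = 17%

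An imbalance of at least 0.3 SD in either direction is 0.3/0.277 = 1.08 standard errors, so it occurs in about 28% of such trials. A baseline t-test at 26 per arm is significant only beyond about 0.46 SD (one-tailed) or 0.56 SD (two-tailed). An imbalance of 0.3 SD would therefore not trigger the protocol's stratified or subgroup analysis.

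**The case against.** The change-score t-test is a valid analysis. Over randomisation it is unbiased with correct type I error; the endpoint is defined as a change, the trial was sized on that test, and the stated N is right. The study calls itself exploratory. The gain depends on a ρ the protocol does not supply. The two RSA recordings use the same device and procedure on the same day, either side of a 30-minute session, which could make ρ high; at 0.9 or more there is almost nothing to gain. An imbalance of 0.3 SD is about one standard error, which the t-test's own standard error already allows for. ANCOVA also does nothing for imbalance in other baseline items. Finally, RSA is computed for each of several stimuli, so the post-value is not yet a single variable.

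Most of this stands as a limit on the claim. The fault is lost efficiency and conditional sensitivity to imbalance, not an invalid test or a wrong N, and the size of the gain is uncertain. It does not remove the point. If ρ is high, ANCOVA costs essentially nothing (80.1% against 80.8% simulated at 0.98); if ρ is moderate, the gain is material. The several-stimuli ambiguity affects the planned t-test equally.

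**Conclusion.** The concern holds. The protocol fixes a valid but less efficient analysis for RSA, EEG amplitude, POMS2 and CAB when the data for a better one are already collected. With 52 analysed and d = 0.7 on the change scale, adjustment raises one-tailed power from 80.1% to between 84.8% and 92.1% for ρ from 0.7 down to 0.3, and by about one point or less for ρ of 0.9 and above. It also removes the linear effect of chance imbalance in the pre-value, which at 0.3 SD and ρ = 0.5 is about a fifth of the assumed effect. These sizes rest on assumed ρ and equal pre and post variances; the direction does not, apart from the single degree of freedom. The measures taken only during the intervention have no matching pre-value in these comparisons and are outside this point. The change should be made, but the planned analysis would not be invalid without it.

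**What to change.** In section 5, item 4) (Main Analysis Methods), replace the t-tests on differences for RSA (primary), EEG amplitude, POMS2 and CAB with a linear model of the post-value on arm, with the same measure's pre-value as covariate (for CAB, the initial score). Report the adjusted mean difference with a 95% confidence interval. Keep the t-test on change as a sensitivity analysis if wished. State which RSA summary across the stimuli enters the primary model, which the planned t-test needs as well.

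Remove the baseline significance tests as the trigger for further analysis. If other baseline variables matter, name them in advance as covariates. Change the test named in section 4, item 3) to match; 58 can stay, since the existing calculation is conservative for the adjusted analysis unless ρ is very high.

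The cost is a protocol amendment to a few sentences and one degree of freedom. It should be made before any outcome data are analysed by arm.

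### Baseline t-tests between randomised groups cannot show balance, and they should not decide whether stratified or subgroup analyses are run

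*Protocol*

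**What the plan says.** Section 5, 4) Summary of analysis, under Main Analysis Methods, sets two linked steps. First: "Unpaired t-tests will be conducted between the two groups to confirm the absence of any differences between the SRI and control groups", applied to the pretest, the initial assessment and the assessment immediately before the intervention. Second, after the between-group comparisons have been listed: "If there is a significant difference between the two groups in the items measured at baseline, stratified or subgroup analyses will be conducted".

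The same part of the protocol sets the level and direction of testing: "The statistical significance level is set at p < 0.05. A one-tailed test is used". It also says that basic and medical information is summarised descriptively. Section 4, 3) fixes the primary comparison as a "two-group comparison (unpaired t-test, one-tailed) of the intervention and control groups" on the pre-to-post change in RSA, and states that "58 subjects will be randomly divided into 29 in the SRI group and 29 in the control group".

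No stratification factor or cut-point is named. The text does not choose between a stratified and a subgroup analysis, gives no multiplicity adjustment, and does not say whether a triggered analysis replaces the primary t-test or is added to it.

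**The concern.** There are four faults in the rule as written.

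- **The test answers no question.** Allocation is random, so a significant baseline difference is a chance finding.
- **Non-significance is read as absence.** In a trial of this size, imbalances large enough to matter will often give p above 0.05.
- **The trigger is the wrong quantity.** What matters is how strongly a baseline variable predicts the outcome. Under the rule, an irrelevant score at p = 0.04 prompts further analyses, while an imbalance in pre-intervention RSA at p = 0.08 does not.
- **A subgroup analysis is not a remedy.** It splits a small sample and leaves the whole-group comparison unadjusted.

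At stake are additional p-values on the primary outcome whose existence depends on chance and whose role is undefined. A reader of the results could not tell which of them was meant to count.

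**Working it through.** **1. The protocol's own sample size.** Inputs from Section 4, 3): "the effect size was set to 0.7, with an alpha error of 0.05 and a beta error of 0.20", one-tailed. The normal approximation gives 26 per arm, 52 in total. The exact noncentral t also gives 52 (power 0.801). This agrees with "resulting in a total sample size of 52 participants". For "considering the possibility of approximately 10% dropout, approximately 58 subjects will be needed": 52 / 0.90 = 57.8, rounded up to 58. The sample size reproduces and is not in dispute. The protocol gives no figure for the chance of a significant baseline item.

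**2. What a non-significant baseline test can show.** With 29 per arm and 56 degrees of freedom, the two-sided 5% critical value is 2.003. An observed difference is significant only beyond 2.003 × √(2/29) = 0.53 SD. By the noncentral t, power is 46% for a true difference of 0.5 SD and 32% for 0.4 SD.

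**3. How many items are tested.** The protocol gives no count, so this is an assumption built from the instruments in Section 5, 3).

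| Set | Items | Count |
|---|---|---|
| Narrow | JSI-mini, AQ, SPQ, four A/ASP scores, one each for CAB, RSA and EEG, POMS2 total only | 3 + 4 + 3 + 1 = 11 |
| Middle | As above, with seven POMS2 scales plus the total | 3 + 4 + 3 + 8 = 18 |
| Wide | Middle set plus age and JART | 20 |

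**4. Chance that at least one item sets off the rule.** With independent items at two-sided 5%, the formula is 1 − 0.95^m.

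- m = 11: 1 − 0.569 = 43%
- m = 18: 1 − 0.397 = 60%
- m = 20: 1 − 0.358 = 64%

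The sidedness is also an assumption. If the one-tailed 5% criterion were applied in whichever direction is observed, each item would have a 10% chance, and 20 items would give 1 − 0.90^20 = 88%.

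**5. Effect of correlation.** Simulated with 29 per arm and 20 equally correlated items:

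| Correlation | Chance of at least one significant item |
|---|---|
| 0.1 | 62% |
| 0.3 | 54% |
| 0.5 | 43% |
| 0.7 | 29% |

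With 18 items correlated only within A/ASP and within POMS2, the chance is 57%, 54% and 49% for correlations of 0.3, 0.5 and 0.7.

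**6. One-sided error for the primary question.** Null simulation with 26 per arm, 20 baseline items, 10,000 trials per setting and median splits on each significant item. The ranges cover independent items, items correlated at 0.3, and one item correlated at 0.5 with the outcome.

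| How triggered results are used | Error rate |
|---|---|
| Primary t-test alone | 5.0–5.5% |
| Stratified test replaces it | 5.3–5.5% |
| Stratified test added, either may count | 5.8–6.3% |
| Any positive subgroup added, either may count | 10.3–11.0% |
| Any positive subgroup replaces it | 9.7–10.0% |

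The Monte Carlo standard error at 5% is √(0.05 × 0.95 / 10,000) = 0.2 percentage points.

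**7. Cost in power of a split.** A half-sample subgroup of 13 per arm has 54% power at an effect size of 0.7 (one-tailed 5%), against 80% for the 26 per arm planned.

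**The case against.** The best defence is that the primary analysis is fixed. Section 4, 3) names it, Main Analysis Methods states the group comparisons without condition, and the triggered analyses are announced as further work. On that reading the primary t-test keeps its 5% error whatever the baseline tests show. The study is also labelled exploratory. This stands, and it limits the severity.

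It also rules out four stronger readings that a reader might infer:

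- **That the baseline p-values choose the final analysis, or that the extra analyses are unplanned.** The text does not say that they replace the primary test, and it does announce them. What it lacks is their factors, cut-points and role.
- **That a trigger is more likely than not.** This needs at least 14 independent items (1 − 0.95^14 = 51%) or a larger set that is only moderately correlated. The POMS2 total is a composite of its seven scales, so those eight scores cannot be independent.
- **That the error rate doubles.** This happens only if any positive triggered subgroup counts as evidence. The protocol states no such success rule and no median split, and the stratified route stays close to nominal.
- **That t-tests are prescribed for gender and handedness.** Basic information is to be summarised descriptively, so this is not established. The same sentence makes the inclusion of age and JART doubtful, which is why 18 is a better upper count than 20.

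None of this gives the baseline tests a valid purpose or makes a p-value a sound trigger. Nor is it a detail left to a statistical analysis plan: the protocol states the rule, and a plan that followed it would inherit the fault.

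**Conclusion.** The point holds as a faulty stated rule and should be fixed. The reasoning about randomisation, absence of evidence and the choice of trigger needs no assumption beyond the text.

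The sizes do rest on assumptions. The chance of at least one trigger is roughly 43% to 64% for 11 to 20 independent items tested two-sided at 5%, and falls to about 29% for 20 items correlated at 0.7. The count, the correlations and the sidedness are not in the protocol. The effect on the one-sided error ranges from almost none (5% to 6% with a stratified test) to about 10% (any positive triggered subgroup counted). The protocol leaves open which applies. The primary t-test, reported alone, remains valid.

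**What to change.** - Delete the baseline t-tests and the sentence that makes stratified or subgroup analyses follow from them. Present baseline characteristics by arm descriptively.
- State that one primary analysis is done in all subjects whatever the observed balance. Preferably this is post-intervention RSA reactivity adjusted for its pre-intervention value, which is already collected. The adjustment is a preference: the change-score t-test is valid under randomisation, and deleting the tests and the rule resolves the fault by itself.
- Label any subgroup look as exploratory and name it in advance as an arm-by-score interaction, for example with A/ASP.

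The cost is a protocol revision, which Section 18 requires to go to the ethics committee. No new data are needed, the analysis work shrinks, and the sample size of 58 can stay.

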1. Initial assessment

Following the preliminary survey, participants will be asked to participate in an initial evaluation. In the initial evaluation, you will be asked to complete (1) Cognitive Assessment Battery (CAB) . (See "3) Observation Items and Schedule"). This will serve as a standard for the temporal assessment of cognitive function of the study subjects before the intervention. This assessment will be conducted on the day before the intervention in order to reduce the burden on the research subjects and to provide potential control data for future multi-week intervention studies on people with mental disorders.

1. Evaluation before the intervention

　On the day following the initial evaluation, participants will participate in a pre-intervention evaluation before the intervention. The evaluation items will be (1) RSA measurement during the Sensory Challenge Protocol (SCP), (2) EEG measurement, and (3) Profile of Mood States 2nd Edition (POMS2). Because the RSA measurement, which is the main outcome of this study, will be conducted at the time point closest to the intervention, the measurements will be conducted in the order of POMS2, EEG, and RSA measurements. These assessments will be used as the basis for a longitudinal evaluation of the subjects' autonomic nervous system function and EEG waveform trends and subjective mood state before the intervention.

1. Intervention

The SRI (Sensory Room Intervention) group will receive an intervention using a sensory room, and the control group will receive 30 minutes of static activity. Of the 58 subjects in the study, approximately 20 subjects who gave their consent will undergo EEG, electrocardiogram (ECG), and pulse wave measurements to determine the degree of relaxation, cognitive activation, and sleep arousal during the intervention (Ref. 13).

≪ Intervention details.≫

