2. EEG measurement: EEG is measured by presenting a task consisting of an oddball task and a Many-standards task^16)^ . The oddball task consists of high-frequency standard stimuli and low-frequency deviant stimuli. The auditory stimuli are designed in the order of frequency and probability of presentation: 1000 Hz, 80% for the standard stimuli, and 1100 Hz, 20% for the deviant stimuli. The Many-standards task has more combinations of frequencies and durations of auditory stimuli than the Oddball task, and the appearance of stimuli is more difficult to predict. The electrode positions are set according to the international 10-20 method, and the sampling frequency is set to 1000 Hz.
3. Profile of Mood States 2nd Edition (POMS2) Japanese version Online version (Ref. 10): A questionnaire designed to assess mood states such as anger, confusion, and depression. It consists of seven scales: Anger-Hostility, Confusion-Bewilderment, Depression-Dejection, Fatigue-Inertia, Tension-Anxiety, Vigor-Activity, and Friendliness. The total mood disturbance (TMD) score, which is a composite of these seven scales, is also calculated. Two types of mood states can be assessed: persistent mood (how the person felt in the past week) and transient mood (how the person feels at the present moment). An all-item version (65 items) for adults will be used. The survey takes approximately 8 to 10 minutes.
4. Items to be retrieved during intervention

　The following items will be obtained during the intervention in approximately 20 subjects who gave consent. The sampling frequency is 1000 Hz.

1. EEG measurement: EEG during the intervention will be measured from 32 electrodes, and the power spectrum of each band will be calculated for each site by frequency analysis using Fast Fourier Transform. The measurement equipment used will be an actiCHamp Plus (PHSIO-TECH), and electrode positions followed the international 10-20 method.
2. ECG and pulse wave measurement: ECG electrodes are guided at three points (right subclavian, left subclavian, and lower chest), and RSA values are calculated from the obtained waveforms. The measurement devices used are actiCHamp Plus (PHSIO-TECH) or PolyPul (Nihonsanteku), a portable pulse wave measuring device.

- Measurement Schedule:

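### The protocol fixes a change analysis for cerebral blood flow, which it never measures, and leaves the in-session EEG and RSA to an unadjusted t-test in about 20 subjects

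*Protocol*

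**What the plan says.** Protocol section 5, part 4, Main Analysis Methods, contains this sentence on a within-session contrast: "For cerebral blood flow, the difference between the mean values at the beginning and end of each 5-minute period in the two groups". It goes on to place the windows at the start and end of the intervention and to compare the groups with an unpaired t-test.

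The next paragraph covers the measures taken during the intervention: "t-tests with no correspondence between groups will be performed for the power spectrum per band of the EEG and the RSA". It names no window, change score or covariate.

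The recordings come from a subset described under Intervention in section 5, part 2: "approximately 20 subjects who gave their consent will undergo EEG, electrocardiogram (ECG), and pulse wave measurements". Section 5, part 3, under the items retrieved during the intervention, lists EEG from 32 electrodes, for which "the power spectrum of each band will be calculated for each site by frequency analysis using Fast Fourier Transform", and ECG with pulse wave, from which RSA is derived. The secondary endpoints include EEG power by band and RSA during the intervention.

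**The concern.** There are two problems.

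First, an analysis is specified for a variable that the trial does not collect. This is not a detail that a statistical analysis plan could fill in, because the protocol states a test for which there are no data.

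Second, the in-session signals that are collected have no reference value. Elsewhere the same section compares RSA, EEG amplitude, POMS2 and CAB between groups as differences from an earlier assessment. In-session EEG power and RSA are compared as they stand. People differ in both for reasons unrelated to the intervention, and in about 20 subjects that variation stays in the error term while chance imbalance at the start goes uncorrected.

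At stake are the precision and clarity of two secondary endpoints, and an analysis in the protocol that cannot be carried out.

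**Working it through.** **1. The plan's own figure.** Section 4, part 3 plans a "two-group comparison (unpaired t-test, one-tailed) of the intervention and control groups", where "the effect size was set to 0.7, with an alpha error of 0.05 and a beta error of 0.20". At 26 per arm the noncentrality is 0.7 × √(26/2) = 2.52 on 50 degrees of freedom, which gives one-tailed power 0.801. At 25 per arm the power is 0.787. So 26 per arm, 52 in total, is right, and 52/0.9 = 57.8 rounds up to 58. Both figures reproduce, and nothing below changes them.

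**2. Where cerebral blood flow appears.**

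| Place in the protocol | Content | Cerebral blood flow? |
|---|---|---|
| Section 5, part 2, Intervention | EEG, ECG, pulse wave during the session | No |
| Section 5, part 3, measurement items | Screening scales, CAB, SCP with RSA, EEG tasks, POMS2, in-session EEG and ECG/pulse wave, with devices for the in-session recordings | No |
| Section 5, part 4, endpoints | RSA, EEG, POMS2, CAB, correlations, in-session EEG power and RSA | No |
| Section 5, part 4, Main Analysis Methods | Start and end windows compared between groups | Yes, once |

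The figures are not reproduced in the text read here, but the written item and endpoint lists leave no place for such a measure.

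**3. Reference value for the in-session signals.** The subtraction of the SCP resting period in Main Analysis Methods concerns the assessments before and after the intervention, not the 30-minute session. No other reference is stated.

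**4. What the unadjusted test can do.** Assumptions: 10 per arm (the protocol gives only about 20 in total), one-tailed alpha 0.05, and d = 0.7 borrowed from the primary outcome for scale.
- Noncentrality 0.7 × √(10/2) = 1.565, 18 degrees of freedom, critical t 1.734. Power is 0.445.
- For 80% power, d would have to be about 1.16.
- The standard error of a chance start difference is √(2/10) = 0.447 SD. The probability of a difference above 0.5 SD is 2 × (1 − Φ(0.5/0.447)) = 0.26. With 29 per arm it is 0.06.

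**5. What a pre-intervention covariate adds.** The effective d is 0.7/√(1 − ρ²), where ρ is the correlation between the baseline and in-session values. The documents do not give ρ, so a range is shown. This is an approximation that keeps 18 degrees of freedom. The change-score column uses 0.7/√(2(1 − ρ)).

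| ρ (assumed) | Unadjusted | Change score | Covariate |
|---|---|---|---|
| 0.3 | 0.44 | 0.36 | 0.47 |
| 0.5 | 0.44 | 0.44 | 0.54 |
| 0.7 | 0.44 | 0.62 | 0.68 |
| 0.8 | 0.44 | 0.77 | 0.81 |

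The covariate helps at every value shown. The change score helps only above 0.5.

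**6. Number of EEG tests.** The band count is not stated, so 4 or 5 is assumed.
- Tested by band only: 4–5 tests × 0.05 = 0.20–0.25 expected false positives if there is no effect.
- Tested by site and band: 32 × 4 = 128 or 32 × 5 = 160 tests, giving 6.4–8 expected.

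**The case against.** The strongest reply is that this is one stray sentence in an exploratory trial, and that a plain comparison between randomised arms is a legitimate analysis of secondary measures. Much of that stands. The protocol makes no power claim for the subset, and the 0.7 was set for a different outcome, so 0.44 indicates scale and is not a broken promise.

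Four stronger readings are tempting, and the documents do not support them.

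- *Person-level differences are confounded with the intervention effect.* In a randomised comparison, stable differences add variance and allow chance imbalance; they do not bias the contrast. Consent to the extra recordings would matter only if it followed allocation and depended on it, and the protocol does not say that it does.
- *The plan tests every electrode in every band.* Power is calculated for each site, but the test sentence and the endpoint speak of bands only. The count of 128–160 is one possible reading.
- *The 5-minute start-to-end contrast should be moved to EEG and RSA.* The first 5 minutes lie inside the intervention, when the researcher is already suggesting stimuli in the SRI group. Adjusting for them, or subtracting them, can remove an early effect. Using only the last 5 minutes would also replace the stated endpoints, which concern the intervention period.
- *Allocation should be stratified by consent to the subset.* Without it, a 7:13 split or worse has probability 0.17 (hypergeometric, 20 drawn from 29 and 29). But a 7:13 split lowers power only from 0.445 to 0.418 and causes no bias, so stratification gains almost nothing.

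**Conclusion.** The point holds in a limited form. The blood-flow analysis cannot be run on the measures the protocol describes; this rests on the text alone and needs no assumption. The sentence may be a leftover, or its windows may have been meant for another signal. The document does not say which.

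The in-session t-test is valid but imprecise. Its power of about 0.44 would rise to about 0.54–0.81 with a pre-intervention covariate if ρ lies between 0.5 and 0.8. That rests on 10 per arm, d = 0.7 and the assumed ρ. A weaker correlation gives a smaller gain, for instance if the two RSA measurements come from different devices, which the protocol permits.

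The multiplicity concern is conditional on site-level testing. The effect is confined to secondary in-session endpoints; the primary RSA comparison and the target of 58 are untouched.

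**What to change.** 1. Delete the cerebral blood flow sentence, or reconcile it with the listed measurement items and endpoints.
2. For in-session RSA, state that the value over the intervention period is compared between arms with the resting RSA from the pre-intervention SCP as covariate. That 3-minute rest is already recorded, and the SCP comes last before the intervention. Preferably derive both values with the same device.
3. For in-session EEG power, adjust in the same way if a comparable pre-intervention value can be taken from the existing recording. That recording is made during auditory tasks, so comparability must be judged first. If it fails, keep the unadjusted comparison and say so.
4. Do not use the first 5 minutes of the session as the reference.
5. State whether EEG power is tested by band only or by site. If by site, average over a few regions named in advance or control the false discovery rate across sites and bands.

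The cost is wording and a slightly different model, with no new measurements and no change to allocation. Section 18 requires a protocol revision to go back to the ethics committee, so the changes are best submitted together.
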